Root canals will be obturated using lateral condensation technique by proper selection of master cone^[[11]](#footnote-11)^ corresponding to the same size as the master apical file, and then a spreader will be used to allow space for auxillary cones, using resin-based root canal sealer^[[12]](#footnote-12)^

- **Outcomes:**
- **Primary Outcomes:**

The pain scale (0-10 scale) consists of a line anchored by two extremes "No pain" and "the worst pain", patients will be asked to choose the mark that represents their level of pain from 0 to 10, Pain level will be assigned as follow:

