# 0 reading represents “no pain”

# 3 readings represent “mild pain”

# 4- 6 readings represent “moderate pain”

# 7- 10 readings represent “severe pain”

- **Secondary Outcomes:**

The quantitative limulus amoebocyte lysate (LAL) test was used to measure endotoxin concentrations in the root canals by a commercial standard kit. The LAL assay is highly sensitive for detection of minute concentrations of endotoxin. LAL is an aqueous extract of blood cells (amoebocytes) from the horseshoe crab, Limulus polyphemus, that reacts with bacterial endotoxin or LPS. This reaction is the basis of the LAL test, which is used for the detection and quantification of bacterial endotoxins.

- **Participant timeline:**

1. Patients will be selected from the clinic of endodontic after eligibility.
2. They will be randomized and pretreatment diagnosed and radiographed at the same visit of treatment.
3. Patients will be treated in two visits and will record preoperative and postoperative degree of pain at 6, 12, 24 and 48hrs.
4. Patients will return pain charts to the operator on the second visit.

| **periods** | **Recruitment** | **Diagnosis** | **Periapical radiograph** | **Randomization** | **Follow up for postoperative pain** |
| --- | --- | --- | --- | --- | --- |
| Zero |  |  |  |  |  |
| 6 h |  |  |  |  |  |
| 12 h |  |  |  |  |  |
| 24 h |  |  |  |  |  |
| 48 h & close out |  |  |  |  |  |

- **Sample Size:**

The aim of this study is to compare the ability of antibiotic paste versus calcium hydroxide used as intra-canal medication in reducing pain and level of endotoxins in necrotic teeth with apical periodontitis. Based on previous study by Ehrmann, et al. (2003), a medium effect size of approximately 0.25 is expected. A total sample size of 24 patients will be sufficient to detect an effect size of 0.25, a power of 80%, and a significance level of 5%. This number has been increased to a total sample size of 28, to adjust for using nonparametric tests. The number is again increased to a total sample size of 36 (18 in each of the two groups) to allow for losses of around 25%. Sample size was calculated using G*Power program (University of Düsseldorf, Düsseldorf, Germany)^[[13]](#footnote-13)^ . minimal clinical difference 3.5 and 4.5 at 24 hrs and 48 hrs respectively.

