# 0 reading represents “no pain”

# 3 readings represent “mild pain”

# 4- 6 readings represent “moderate pain”

# 7- 10 readings represent “severe pain”

Secondary outcomes will be collected by the operator by commercial standard kit then stored at -80^0^ C so that all samples would be processed at the same time by LAL assay for quantification of bacterial endotoxins.

- **Statistical analysis:**

Data will be analyzed using IBM SPSS advanced statistics (Statistical Package for Social Sciences), version 21 (SPSS Inc., Chicago, IL). The level of endotoxins will be described as mean and standard deviation. The level of pain will be described as median and range or interquartile range, as appropriate. The level of endotoxins will be explored for normality using Kolmogrov-Smirnov test and Shapiro-Wilk test. If the exploration of data reveals that the collected values are normally distributed, a 2-way ANOVA with repeated measures will be performed to compare between the 2 groups and the change with time. If the interaction between the groups and time is found to be significant, a 1-way repeated measures ANOVA will be used to examine significant differences between time periods within each of the two groups. The Student’s t-test will be performed to test the significance between the two groups at each time period. If the exploration of data reveals that the level of endotoxins is not normally distributed and for the analyses of the pain score, Mann-Whitney U test will be performed to test the significance between the 2 groups at each time period. Friedman’s test followed by multiple comparisons test will be performed to test the significance between the 4 time periods within each group. In addition, correction of p-value will be done using Bonferroni adjustment to avoid hyperinflation of type 1 error that arises from multiple comparisons. A p-value less than or equal to 0.05 will be considered statistically significant. All tests will be two tailed. The effect size will be measured using standardized mean difference.

- **Data monitoring:**

There will not be a Data Monitoring Committee for the following reasons:

- Interim analysis is not involved in the trial so periodic inspection of the accumulating outcome data is not required.
- Short duration of the trial.
- Minimal risks of the trial.
- **Harms**

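### The claim that 24 (28) patients give 80% power for an effect of 0.25 does not hold for the planned Mann-Whitney comparison of pain, and the metric, test, time point and SD behind it are not stated

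*Protocol*

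**What the plan says.** Under Sample Size, the protocol cites an earlier study of intracanal medicaments and states that "a medium effect size of approximately 0.25 is expected". It continues: "A total sample size of 24 patients will be sufficient to detect an effect size of 0.25, a power of 80%, and a significance level"; the level given there is 5%. Then: "This number has been increased to a total sample size of 28, to adjust for using nonparametric tests". A last step takes the total to 36, or 18 per group, for losses of about 25%. The paragraph ends with "minimal clinical difference 3.5 and 4.5 at 24 hrs and 48 hrs respectively". It credits G*Power but does not say which test was chosen there, whether 0.25 is d, f or something else, at which time it applies, or what SD was assumed.

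The primary outcome is pain on a numerical scale; under Primary Outcomes, "patients will be asked to choose the mark that represents their level of pain from 0 to 10". Under Statistical analysis, the between-group method for pain is this: "Mann-Whitney U test will be performed to test the significance between the 2 groups at each time period". All tests are two-tailed. A Bonferroni adjustment is planned, with the number of comparisons not given. Repeated-measures ANOVA is planned only for endotoxin, the secondary outcome, and only if those data look normal. The effect size is to be reported as a standardized mean difference.

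**The concern.** A stated power has meaning only for a given effect, test and sample size. Here the effect is a bare 0.25, and the test behind the calculation does not appear to be the one planned for the primary outcome. Calling 0.25 medium fits the usual convention for Cohen's f; a medium d is 0.5. The planned standardized mean difference, however, points to d.

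The same paragraph also gives differences of 3.5 and 4.5 points, which on a 0-10 scale are far larger than a quarter or half of any attainable SD. A reader cannot tell which effect the trial was sized for. If the result is not significant, the paragraph would support the statement that an effect of 0.25 had an 80% chance of being detected. For the test in the plan, that is not so.

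**Working it through.** **Inputs from the protocol.** Effect 0.25; total N of 24, then 28, then 36; power 80%; two-sided alpha 5%; 1:1 allocation; four postoperative readings (6, 12, 24 and 48 h); 0-10 scale; minimal clinical differences 3.5 (24 h) and 4.5 (48 h).

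**Assumptions not in the protocol.** Correlation 0.5 between readings and sphericity, for the ANOVA. Normal data with a shift and equal SDs, for Mann-Whitney power.

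**1. Reproducing 24.** For the group-by-time interaction, with m readings and correlation ρ, the noncentrality is λ = N f² m / (1 − ρ).
- N = 24: λ = 24 × 0.0625 × 4 / 0.5 = 12, on F(3, 66); power 0.816.
- N = 22: λ = 11, on F(3, 60); power 0.775.

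So 24 is the smallest even total that reaches 80%. The within-subject (time) effect gives the same N. The match depends on the assumptions: ρ = 0.3 gives 32 and ρ = 0.7 gives 16; at ρ = 0.5, three readings give 28 and five give 22.

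Other calculations do not give 24:
- Between-group effect of the same ANOVA: λ = N f² m / (1 + (m − 1)ρ) = 24 × 0.0625 × 4 / 2.5 = 2.4; power 0.32 at N = 24, 0.36 at N = 28; 82 in total needed for 80%.
- Two-sample t-test, two-sided: 64 per arm for d = 0.5, 253 per arm for d = 0.25.

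The two inflation steps are roughly in order: 24 × 1.15 = 27.6 and 24 / 0.85 = 28.2, against 28; 28 × 1.25 = 35 and 28 / 0.75 = 37.3, against 36.

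**2. Power of the planned test for 0.25.** For two equal groups d = 2f, so f = 0.25 means d = 0.5. Simulated two-sided Mann-Whitney power at one time (20,000 runs):

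| Per arm | d = 0.5, alpha 5% | d = 0.25, alpha 5% | d = 0.5, alpha 1.25% | d = 0.25, alpha 1.25% |
| --- | --- | --- | --- | --- |
| 12 | 19% | 8% | 7% | 2% |
| 14 | 22% | 9% | 9% | 3% |
| 18 (no losses) | 29% | 11% | 12% | 3% |

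The 1.25% columns assume that Bonferroni covers the four time points (0.05 / 4), which the protocol does not say. With the usual Mann-Whitney efficiency of 0.955, 80% power at 5% needs about 64 / 0.955, or 68 per arm, for d = 0.5, and 253 / 0.955, or 265 per arm, for d = 0.25.

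**3. Can 0.25 match 3.5 and 4.5 points?** On a 0-10 scale the variance at mean μ is at most μ(10 − μ). With equal SDs and means D apart, the common SD is largest when the means lie at 5 ± D/2:
- D = 3.5: √(3.25 × 6.75) = 4.68, so d ≥ 3.5 / 4.68 = 0.75.
- D = 4.5: √(2.75 × 7.25) = 4.47, so d ≥ 4.5 / 4.47 = 1.01.

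To give d = 0.25 the SD would have to be 3.5 / 0.25 = 14 or 4.5 / 0.25 = 18; to give d = 0.5, it would have to be 7 or 9. None is attainable.

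An interaction f is a different quantity. Suppose the group differences are 0, 0, 3.5 and 4.5 over the four times (mean 2). The half-deviations are −1, −1, 0.75 and 1.25, with root mean square √(4.125 / 4) = 1.016. Then f = 0.25 at an SD of 1.016 / 0.25 = 4.1, which the scale allows.

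**4. Power for 3.5 and 4.5 points.** Approximate Mann-Whitney power with 14 per arm at 5% (noncentral t with n × 0.955), by assumed SD:

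| SD | 3.5 points | 4.5 points |
| --- | --- | --- |
| 2.0 | 0.99 | 1.00 |
| 2.5 | 0.94 | 0.99 |
| 3.0 | 0.83 | 0.96 |
| 3.5 | 0.70 | 0.89 |
| 4.0 | 0.59 | 0.80 |

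Simulation runs slightly lower: for 3.5 points, 0.81 at SD 3.0 and 0.78 at SD 3.1. At alpha 1.25%, about 80% is reached for 3.5 points at an SD of about 2.5.

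**The case against.** The strongest reply is that the protocol never calls 0.25 a between-group effect at one time. If it is an interaction f, the SD bound does not apply and the value can sit beside 3.5 and 4.5 points, as step 3 shows. Moreover, 0.25 is the effect expected, whereas 3.5 and 4.5 are called minimal clinical differences, and nothing says that 24 was derived from them. All of this stands. A reader might infer that 0.25 is flatly impossible on this scale; the documents support that only for a between-group effect at a single time.

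Nor is it established that an interaction was used in G*Power. A within-subject effect gives the same 24, and both need a correlation that the protocol does not state.

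Neither point rescues the power claim. The plan for pain contains no interaction test, and a within-subject effect says nothing about antibiotic paste against calcium hydroxide. An allowance from 24 to 28 for nonparametric testing does not turn either calculation into a group comparison at one time.

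A further objection is that 28 evaluable patients may be quite enough for 3.5 to 4.5 points. That also stands, subject to the SD, and it limits the remedy to rewording.

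**Conclusion.** The statement that 24 (28) patients give 80% power for an effect of 0.25 is wrong for the planned between-group analysis of pain. At 12 to 14 per arm the two-sided Mann-Whitney test at one time has about 19-22% power if 0.25 is Cohen's f and about 8-9% if it is d. It stays at or below 29% even with all 36 patients evaluable. These figures assume normal data with a shift. They fall further if Bonferroni is taken to cover the four times. As a single-time between-group effect, 0.25 is also incompatible with the two point differences in the same paragraph.

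A reader might go on to infer that the trial is too small for 3.5 to 4.5 points. The documents do not support that. They give no SD; at 14 per arm, power for 3.5 points is about 80% or more up to an SD of about 3.0 and drops to about 59% at an SD of 4. Whether the size is adequate turns on an input the protocol leaves out. The cited earlier study was not available, so the origin of 0.25 could not be checked.

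**What to change.** Keep 36 patients. Delete the claim that 24 (28) patients give 80% power for 0.25, and rewrite the Sample Size paragraph for the two-sided Mann-Whitney test. It should name:
- the time point on which the sample size rests;
- the alpha for that comparison, and whether Bonferroni covers the four times;
- the target difference in scale points (3.5 or 4.5, and why);
- the assumed SD with its source.

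As a guide under a normal shift, 14 evaluable patients per arm give about 80% power for 3.5 points if the SD is about 3.0 or less at 5%, or about 2.5 or less at 1.25%. These limits are solved backwards from the planned size and vary with the shape of the scores, so they should not stand in for a sourced SD. If the sourced SD is larger, the paragraph should state the lower power or the larger detectable difference.

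The cost is one rewritten paragraph and a larger stated detectable effect. No further patients are needed for this correction.

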# Recruitment:

Patients are recruited for our clinical trial from the clinic of endodontic at the faculty of oral and dental medicine, Cairo University to meet the target sample size.

- **Randomization:**

1. **Sequence generation :**

A random sequence will be generated by computer software,

(http://www.random.org/).

The table will be kept with the assistant supervisor.

1. **Allocation concealment mechanism :**

- Eight folded numbered papers will be packed in opaque sealed envelopes to be dragged by the patients.
- After instrumentation, operator will open the envelope and use the intra-canal medication assigned to that patient. The opaque envelopes will contain the numbers of each random sequence for both groups (AP for experimental group) and (Ca (OH)_2_ for control group).

# Implementation:

The assistant supervisor or co-investigator is the one who will generate the random sequence, assign the participants to the intervention or control groups and the only one who knows whether A or B represents the intervention or the control group.

**Blinding:**

- The study will be double- blinded which is participants and the assessor.
- Participants will not know which group they will be treated with after they will choose the folded paper inside the opaque envelopes which contain the numbers of each random sequence for both groups.
- Assessor who will assess all results data will not know which group the participants related to (fig.8).
- **Data collection, management, and analysis**
- Baseline Data collection:
- Baseline data will be collected by the operator through a report (Fig.1-5), which comprises of 2 charts (one concerning general health and one concerning the chief complaint related events).
- The report will be anonymous where patients identified by their serial numbers (the first letter of the first and last name and date of birth) only will be registered.
- The full detailed personal data of the patient will be written in a separate sheet having the patient's serial number for further contact with patient, this sheet can be only seen by the operator and the assistant supervisor.
- Outcome data collection: (Fig 6, 7)

Primary outcomes will be collected by the operator through (NRS) which is reliable and valid tool (Brunelli et al, 2010). It is scale consisting of numbers from 0 to 10:

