A 2-stage access cavity preparation will be performed. The first stage involved the removal of caries without exposure of the pulp chamber by using a high-speed diamond bur. In the second stage, before entering the pulp chamber, the access cavity will be disinfected according to the decontamination protocol described previously. A new bur will be used to access the canal.

1. 1^st^ sample:-

The first endotoxin sample will be taken by introducing the paper points^[[2]](#footnote-2)^ into the full length of the canal (determined by radiographs and apex locator^[[3]](#footnote-3)^) and retaining them in position for 60 seconds. Next, the paper points will be placed in a glass tube and stored at -80^0^C for the LAL assay.

1. Preparation:-

-The root canals will be prepared with Gates-Glidden drills^[[4]](#footnote-4)^ sizes 4, 3 and 2 for the coronal part, and rotary Irace instruments^[[5]](#footnote-5)^ using an endodontic motor^[[6]](#footnote-6)^ with adjusted torque and speed according to the manufacturer's instructions. The rotary files will be introduced inside the canal using EDTA gel^[[7]](#footnote-7)^.

-Before the use of each instrument, irrigation with a syringe (27-G needle) Containing 3ml 2.5% sodium hypochlorite^[[8]](#footnote-8)^.

- Subsequently, 5% sodium thiosulfate will be used to inactivate NaOCl. Then, 5ml saline solution to wash the canal.

1. 2^nd^ sample:-

The second endotoxin sample will be taken as previously described just after the irrigation with saline solution.

1. Intracanal medication:-

The canals will be dried with paper points and filled with intracanal medication plugged into the canal by using Lentulo spiral^[[9]](#footnote-9)^ . The access cavities will be properly filled with Cavit^[[10]](#footnote-10)^.

- **Control group:** Ca (OH)_2_ Paste.
- **Experimental group:** antibiotic paste (ciprofloxacin, metronidazole)

1. The patient will be instructed to record his/her pain level on the pain scale chart after 6 h, 12 h, 24 h and 48 h.
2. 3^rd^ sample:-

After 7 days of intracanal medication, the canal will be accessed under rubber dam isolation by using the protocol for disinfection described previously. The medication will be removed, the final endotoxin sample will be taken just after the irrigation with saline solution.

1. Obturation:-

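### The operator, who knows the treatment arm, handles the pain charts before the blinded assessor, and nothing protects the primary outcome in between

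*Protocol*

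**What the plan says.** All references are to the protocol.

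- **Who is blinded.** Under Blinding: "The study will be double- blinded which is participants and the assessor". The same section adds: "Assessor who will assess all results data will not know which group the participants related to". The operator is not listed as blinded.
- **Who knows the arm.** Under Allocation concealment mechanism, once instrumentation is finished, the "operator will open the envelope and use the intra-canal medication assigned to that patient". The groups are labelled by product: "AP for experimental group) and (Ca (OH)_2_ for control group".
- **Who is said to hold the code.** Under Implementation, the assistant supervisor or co-investigator is "the only one who knows whether A or B represents the intervention or the control group".
- **Who scores the pain.** Under Sequence of Procedural steps: "The patient will be instructed to record his/her pain level on the pain scale chart", at 6, 12, 24 and 48 hours.
- **Who collects the scores.** Under Outcome data collection: "Primary outcomes will be collected by the operator through (NRS) which is reliable and valid tool". Under Participant timeline: "Patients will return pain charts to the operator on the second visit".
- **The forms.** The patient's chart (Figures 6 and 7) has fields for patient name, patient number, doctor's name and doctor's telephone number. The assessor chart (Figure 8) is a separate form, headed by patient number, with a score for each of the four time points.

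**The concern.** The primary outcome is a subjective 0-10 rating written on paper by the patient. Blinding the patient protects the act of rating. Blinding the assessor protects what is done with the scores once the assessor has them. Between these two points the chart goes to the operator, who knows which paste was placed.

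Several things can happen at that point. A mark between two numbers may need interpreting, a blank reading may prompt a question to the patient, and a score has to be copied from the patient's chart to the assessor chart. If someone who knows the arm does any of these, the result can lean towards one arm without anyone intending it. The statistical analysis cannot repair this afterwards, because the altered or completed entry is the only record.

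**Working it through.** No arithmetic decides this point. It rests on setting the protocol's statements about roles side by side.

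**Step 1: does the operator know the arm?** Yes, on the Allocation concealment text. The operator opens the envelope, the groups are named AP and Ca(OH)2, and the operator places the assigned product. No coded or masked supply of the two pastes is described. The Implementation section says only one other person knows what A and B stand for. The two statements cannot both hold as written.

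**Step 2: who rates pain, and when relative to allocation?** The patient rates. The preoperative score is recorded before any intervention, and the envelope is opened only after instrumentation, so the baseline rating is made before the operator knows the arm. The 6 to 48 hour ratings come after allocation, but a patient stated to be blinded makes them.

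**Step 3: what route do the scores take?**

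| Step | Person | Aware of arm? | Safeguard stated |
| --- | --- | --- | --- |
| Marks the chart | Patient | No (stated) | Blinding of participants |
| Receives the chart at visit 2 | Operator | Yes | None |
| Queries unclear or blank marks | Not stated | Not stated | None |
| Copies scores to Figure 8 | Not stated | Not stated | None |
| Assesses the data | Assessor | No (stated) | Blinding of assessor |

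The protocol does not say how a chart gets from operator to assessor, nor that these are two people. The Auditing section lists enrolment, consent, eligibility, allocation and adherence; it does not list outcome data.

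**Step 4: how much passes through this step?** The planned maximum is 36 patients (Sample Size) with four postoperative readings each: 36 × 4 = 144 readings. This counts readings handled, not readings biased. Only those that are unclear, blank or wrongly copied are open to influence, and the protocol gives no rate for any of these.

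**Step 5: how long after the last reading is the chart returned?** If readings run from placement of the medication, as the order of the procedural steps implies, the last is at 48 hours (2 days) and visit 2 follows 7 days of medication: 7 − 2 = 5 days. If they run from obturation, as the text under the outcomes table says, they fall after visit 2 and a chart handed in at visit 2 could not be complete. The five-day gap therefore depends on the first reading of an unresolved conflict, and the point made here does not rely on it.

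**The case against.** The strongest reply is that nothing here breaks the blinding claimed. The protocol limits that claim to participants and the assessor. The rater is the blinded patient, and the scores should be on paper before the operator sees them. A separate blinded assessor with a separate form is foreseen. Collecting completed self-report charts is compatible with all of this, and no text says that the operator queries, clarifies or completes entries.

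Most of this stands, and it rules out some stronger readings:

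- A reader might infer that outcome assessment is in fact unblinded and the double-blind label false. The documents do not support that, because the operator is never called blinded and does not rate the pain.
- A reader might infer that a small shift in scores would decide the trial. The documents give no basis for it. The only differences they name as clinically minimal are 3.5 at 24 hours and 4.5 at 48 hours, and no size of shift can be derived.
- A reader might extend the point to the endotoxin samples, which the operator also collects. Nothing says that the tubes show the arm, and they are measured by a quantitative kit assay in one batch.

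The reply does not close the gap. Compatibility with blinding depends on the operator only carrying the chart, and the protocol does not limit the operator to that. The stated role is to collect the primary outcome, the handover to the assessor is not described, and the two roles are not said to be separate.

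**Conclusion.** The point holds as a weakness in the handling of the primary outcome, not as a contradiction of the blinding statement. A person who knows the arm receives a subjective outcome before the blinded assessor does, and no safeguard is stated for unclear marks, blank readings or transcription. The size and direction of any bias cannot be derived from the documents.

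This rests on two assumptions: that the operator recognises the arm from the envelope or the product, as the Allocation concealment text implies, and that the charts follow the return route given in the timeline.

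The firm inconsistency is a different one: Implementation gives knowledge of the code to one person only, while Allocation concealment requires the operator to act on a product-named assignment. It should be corrected together with the return route, because a reader cannot otherwise tell who is unblinded.

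The change is worth making before charts are collected: it is cheap and removes a route to bias.

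**What to change.** 1. **Participant timeline and Outcome data collection:** replace return to the operator with return of the completed chart, in a sealed envelope identified by study number only, to the blinded assessor.
2. **Blinding:** state that the assessor is not the operator.
3. **Outcome data collection:** state that the assessor checks the chart and transcribes it to Figure 8, and that blank readings are not completed retrospectively. This is a rule for data collection; how missing readings are analysed can stay with the statistical analysis plan.
4. **Figures 6 and 7:** remove the patient-name field from the returned chart. The patient-number field already there is enough to link it.
5. **Implementation and Allocation concealment:** reconcile the two. Say plainly that the operator learns the assignment when the envelope is opened, and list everyone who knows it.

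The cost is protocol wording, a revised chart and envelopes, plus small logistics at visit 2, since the assessor or a sealed drop box must be available. The assessor's role and form are already in the protocol, although it does not say that this person attends visit 2. Sample size and statistical tests are unaffected.
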